#### Physical Activity

We chose to assess physical activity with two brief questions: one on the amount of time the participants spent in moderate-to-vigorous physical activity, and one on whether their amount of physical activity had changed since the pandemic.

#### Health History Checklist

The relationship among stress, major life events, and other biopsychosocial factors has a long history of study in epidemiology and public health, with a sound mechanistic basis [52,53,54]. We hypothesized that the effects of working in the challenging circumstances of the COVID-19 pandemic would have effects on health over time. We obtained a comprehensive history of the participants’ mental and physical health during the pandemic to enable prospective evaluation of incident conditions.

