The effects of stress on long-term physical and mental health can take many years to become manifest. Military combat deployment [23,24] and elevated symptoms of posttraumatic stress disorder (PTSD) in civilians have been associated with increased risk of hypertension, myocardial infarction, and stroke [25,26]. Longitudinal trends show that the likelihood of developing multiple physical symptoms over time is higher for those who were deployed in combat than those without combat experience [27].

Research on the effects of stress on the COVID-19 workforce [9,18] is underway but is in its early stages [28], with mixed results [29]. Some studies have noted the potential importance of resilience in response to stress, including in health care workers [30], but adequate supporting data on the role of resilience in response to stress are lacking [31]. The COVID-19 pandemic experience of essential workers provides an opportunity to develop new information on the influence of sustained stress on the short- and long-term physical and mental health of the workforce involved in providing health care or to support health care personnel, as well as on the potential influence of aspects of resilience and its role in moderating the effects of stress.

Based on the extensive body of literature on the psychosocial influences on health, it is likely that the COVID-19 pandemic will have deleterious effects on the health of health care workers and support staff in a broad range of professions [32]. Over time, as COVID-19 treatments and management improve and infection rates decrease through public health measures and vaccination, we anticipate that sources of stress will decrease, resulting in a gradient of influence on health among health care workers who enroll in the COVID-19 Study of Healthcare and Support Personnel **(**CHAMPS) during later phases of the pandemic. The CHAMPS Study and Registry is designed to ascertain the time course and magnitude of these changes on the long-term mental and physical health of essential workers in the health care environment.

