### Objectives

The objective of the CHAMPS Study and Registry is to assess the short- and long-term physical, social, and behavioral health of personnel (“essential workers”) involved in supporting or delivering care for patients with COVID-19. Included are first responders, maintenance and support staff working in clinical settings, and health care professionals of all specialties and services. At enrollment, baseline data were obtained on the study participants’ working environment, lifestyle, and mental and physical health. Subsequent waves of data collection will obtain follow-up information after 6 months and then annually through 2024. The study was approved by the Villanova University Institutional Review Board (IRB) in May 2020.

The primary objectives of the CHAMPS study are to (1) determine the extent to which working in health care affects future physical and mental health; (2) evaluate trends over the time course of the evolving pandemic; (3) identify exposure variables that are associated with incident changes in health over time; and (4) identify factors that influence short- and long-term health. Specific hypotheses include the following:

Measures of mental health symptoms of anxiety, traumatic stress, depression, insomnia, disordered eating, resilience, burnout, and poor self-reported health will be more prevalent in essential workers than in the general population and greater in magnitude than reported in similar populations before the COVID-19 pandemic.The severity of mental health symptoms will be associated with prevalence of SARS-CoV-2 infection rates in the geographic region in which the study participants work.Mental health symptoms will persist longer among study participants with more severe symptoms.Essential workers who report elevated symptoms of anxiety, traumatic stress, or depression will experience exacerbation of existing physical health conditions over time and higher incidence of new physical health conditions.Severity and progression of mental and physical health conditions will be exacerbated by the degree of perceived exposure to adverse working environments, such as availability of personal protective equipment, extended working hours, and adequacy of staffing levels.

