### Participants and Recruitment

Eligible participants were adult essential workers involved in health care. For the purposes of the CHAMPS study, essential workers were defined as adult (aged 18 years or older) health care personnel, support personnel, and first responders working in any health care facility or in the community. Included were those working in facilities that are involved in patient care, such as hospitals, clinics, private practices, or screening facilities; those directly involved in patient care (eg, physicians, nurses, phlebotomists, respiratory therapists, pharmacists); laboratory staff; service employees (office staff, maintenance, housekeeping, food service); individuals working in long-term care facilities; and first responders (eg, police officers, firefighters, emergency medical technicians, paramedics). Collectively, we refer to these as “essential workers.” Enrollment took place over 13 months, from May 2020 through June 2021, throughout the United States.

Recruitment included advertising through local and national professional and trade organizations, news, social and professional media, alumni organizations, and word of mouth to describe the study and disseminate the internet link that provided access to the informed consent form and study questionnaires. Professional and trade organizations were identified and contacted. Website posts, e-newsletters, and social media were used to reach members of eligible occupations, with news or social media posts either by their group administrators or by the study team. The wider social media universe was reached through posts on university channels on various platforms, university-affiliated influencer posts, and a limited paid media campaign. Social media posts and outreach to organization leaders continued periodically throughout the recruitment period.

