#### Six-Month Follow-up

The first follow-up occurred 6 months after enrollment and completion of the baseline questionnaire. Assessments included resilience, burnout, eating habits, and alcohol and substance use; physical activity; nutrition; height, weight, and weight discrimination items [41,42]; and a comprehensive health history checklist.

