#### Alcohol and Substance Use

We hypothesized that alcohol and substance use may increase in response to the stress of workplace demands, but we thought that a thorough screening would not be in the best interest of the overall study. We decided to limit our data to answers to two questions, namely, whether the participants’ alcohol and substance use increased, was unchanged, or decreased since the start of the pandemic.

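### The health checklist first given at T1 looks back to the pandemic and not to enrolment, so T1 reports cover windows that differ by 13 months between first and last enrolees and include time before baseline

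*Protocol article*

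**What the plan says.** Three statements in the article's Methods set the timing.

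- **Enrolment** (Participants and Recruitment): "Enrollment took place over 13 months, from May 2020 through June 2021, throughout the United States".
- **T1** (Six-Month Follow-up): "The first follow-up occurred 6 months after enrollment and completion of the baseline questionnaire". The T1 content ends with "and a comprehensive health history checklist".
- **Look-back** (Health History Checklist): the history covers "mental and physical health during the pandemic to enable prospective evaluation of incident conditions".

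Table 1 ticks the checklist at T1 to T5 and not at T0. Enrolment items cover self-reported general health and infection status, but no list of conditions is described at that point.

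Two further statements bear on how the reports would be used. The Rationale expects stress to lessen as the pandemic is brought under control, "resulting in a gradient of influence on health among health care workers who enroll" in later phases, and one primary objective is to "evaluate trends over the time course of the evolving pandemic". Under Data Management and Quality, new health events from follow-up are to be related to variables measured at baseline. Aim 4 asks whether mental health symptoms go with a higher incidence of physical conditions.

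**The concern.** The look-back begins at a calendar event and ends at a personal date. With staggered enrolment, its length is therefore a function of enrolment date. Two consequences follow if T1 reports are used as outcomes.

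1. **Unequal time at risk.** Someone who enrolled late has had longer to acquire a condition that counts. At equal risk, T1 reports rise with enrolment date, whereas the Rationale expects the influence on health to weaken with enrolment date. A real gradient could be masked or reversed. Adjusting a phase comparison for enrolment date does not help, because enrolment phase is the contrast of interest.
2. **Lost time order.** The window opens before T0. On the description given, a condition that began before the baseline questionnaire cannot be told apart from one that followed it. An association between baseline symptoms and a supposedly incident condition may then run the wrong way, most often among late enrolees.

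**Working it through.** **Inputs from the article.** First enrolment is May 2020 and last is June 2021. T1 is enrolment plus 6 months, so it falls between November 2020 and December 2021. The stated 13-month enrolment period reproduces: June 2021 minus May 2020 = 13 months.

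**Assumption.** No date is fixed for the start of the pandemic. The Background gives a first report in early January 2020, a first US case two weeks later, and a steep rise by early spring. I take March 2020 and show January to April.

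**Step 1: windows.** Window = (enrolment month + 6) − start month. Time before T0 = enrolment month − start month.

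| Assumed start | First enrolee (months) | Last enrolee (months) | Difference | Ratio | Share before T0, first | Share before T0, last |
|---|---|---|---|---|---|---|
| Jan 2020 | 10 | 23 | 13 | 2.3 | 4/10 = 40% | 17/23 = 74% |
| Feb 2020 | 9 | 22 | 13 | 2.4 | 3/9 = 33% | 16/22 = 73% |
| Mar 2020 | 8 | 21 | 13 | 2.6 | 2/8 = 25% | 15/21 = 71% |
| Apr 2020 | 7 | 20 | 13 | 2.9 | 1/7 = 14% | 14/20 = 70% |

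The 13-month difference does not depend on the start date. The lengths, ratios and shares do.

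**Step 2: effect on a yes/no report.** With a constant hazard, risk over m months = 1 − (1 − r)^(m/12), where r is the annual risk. The values of r are illustrative assumptions, and the start is March 2020.

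| Annual risk r | First enrolee, 8 months | Last enrolee, 21 months | Ratio |
|---|---|---|---|
| 2% | 1.3% | 3.5% | 2.60 |
| 5% | 3.4% | 8.6% | 2.55 |
| 10% | 6.8% | 16.8% | 2.48 |
| 20% | 13.8% | 32.3% | 2.34 |

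**Step 3: what would cancel it.** Reports are equal when the average hazard times the window is equal. The last enrolees' average hazard must then be 8/21 = 0.38 of the first enrolees'. For January the figure is 10/23 = 0.43, and for April 7/20 = 0.35. In calendar terms, the last enrolee's window contains the whole of the first enrolee's. If both groups had the same hazard in the shared 8 months, a ratio of 0.38 means no hazard at all in the remaining 13.

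**Step 4: equal windows.** If the item were tied to T0, the T1 window would be 6 months for everyone and none of it would precede baseline.

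**The case against.** The strongest reply is that T1 is not meant as an incidence outcome. The Health History Checklist section says the history was taken so that incident conditions could be evaluated later, and Annual Follow-up Questionnaires places incidence in the annual waves. T1 would then be the reference that separates existing from new conditions, and incidence at T2 to T5 would be largely unaffected. This reading is fair and it limits the point. It does not remove it: T1 counts still cannot be compared across phases, who is classed as already having a condition still depends on a window of unequal length, and events between T0 and T1 drop out of incidence.

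A second reply is that the item wording is not shown and onset dates might be collected. That also stands, so the finding rests on the checklist as described. A third is that no aim explicitly compares T1 checklist counts by enrolment phase. That is true. However, the Rationale builds the expected gradient into what the study is designed to ascertain, and the use of incident events with baseline variables is stated.

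A reader might infer that the other T1 items looking back to the pandemic rise with enrolment date in the same way. The documents do not support this. The alcohol and substance questions ask whether "alcohol and substance use increased, was unchanged, or decreased since the start of the pandemic", and one of the two activity questions asks "whether their amount of physical activity had changed since the pandemic". These record a direction of change and do not accumulate events. Only their recall distance varies with enrolment date.

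**Conclusion.** The point holds for the health history checklist, on its description in the article. The T1 look-back differs by 13 months between first and last enrolees under any start date: 8 v 21 months if March 2020 is assumed, and 7–10 v 20–23 months across January to April 2020. With a March start, about 25% to 71% of the window precedes T0.

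What follows depends on use. If T1 reports are counted as incident or compared by phase, later enrolees are expected to report more, by a factor of roughly 2.3 to 2.6 at a constant hazard with a March start. This is an expectation and not a certainty, since an average hazard down to about 0.38 would offset it. If T1 is only the reference for T2 to T5, the damage is confined to T1 counts, to the classification of existing conditions, and to lost T0–T1 events.

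A reader might go further and predict how counts of new conditions should fall or rise from wave to wave under constant risk. The article states no look-back for T2 to T5, so no such figures can be derived.

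**What to change.** - **Collect onset.** At the next wave, ask month and year of onset for each checked condition, including those already reported at T1. Annual Follow-up Questionnaires allows items to be added.
- **Define the terms.** State the checklist's recall period at each wave, the date taken as the start of the pandemic, and the reference point for incident.
- **Count incident conditions from T0.** Only onsets after T0 qualify. Earlier onsets are existing conditions. Where onset stays unknown, treat the time as interval-censored over the period the report covers.
- **Compare on person-time.** Compare enrolment phases and waves as rates over equal follow-up, or with the log of months covered as an offset. Do not use raw T1 checklist counts as evidence for or against the phase gradient.

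The cost is one date field per condition in a web questionnaire and some revised analysis wording. The downside is recall error in the onset month, largest for conditions reported at T1, and wider intervals for the phase comparison because onsets before T0 no longer count.

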### Exposure Assessment

We will define and quantify exposure to COVID-19 service burden by summing participants’ scores on the Perception of Stress at Work scale developed by Wu and colleagues [4] in 2009 during the SARS pandemic, and we will add a point to that score for each of several additional stressors: (1) working more hours since the pandemic; (2) working in a different setting; (3) caring for patients with COVID-19; (4) changing one’s living arrangement; (5) receiving a COVID-19 diagnosis; and (5) having a close contact (friend, family member, colleague, or any loved one) with a COVID-19 diagnosis (Table 2).

For this purpose, perceived stress was deemed to be an outcome of exposure, but it can also be included as an exposure variable in models that ascertain incidence of health conditions over time.

**Table 2 table2:** Components of the algorithm-based score for exposure to COVID-19 service burden.

Component	Scoring
Perception of Stress at Work scale	Score of 9-item scale
Working more hours	Yes=1 additional point
Working in a different setting	Yes=1 additional point
Caring for patients with COVID-19	Yes=1 additional point
Changing one’s living arrangement	Yes=1 additional point
Receiving a COVID-19 diagnosis	Yes=1 additional point
Having close contact (friend/family member/colleague/any loved one) with a COVID-19 diagnosis	Yes=1 additional point

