### Analysis

#### Data Management and Quality

Data are collected through the web-based Qualtrics system. SPSS (IBM Corporation) and SAS (SAS Institute, Inc) will be used for data analysis. Initially, we will perform an exploratory analysis to establish patterns of missingness and distributions of the variables being measured. The registry data will be characterized with descriptive analyses, including frequency distributions, prevalence rates of COVID-19 testing and SARS-CoV-2 infection, and means and standard deviations of scores on the scales measuring work environment, general health status, anxiety, depressive symptoms, social support, traumatic stress, social support, sleep quality, and stress. Multiple logistic and linear regression methods will be used to assess baseline associations of health and well-being with estimates of exposure to COVID-19 infection and COVID-19–related stress at work. Models will be adjusted for sex, age, race/ethnicity, and job classification. Other preliminary explorations of associations between measured variables will be performed to aid the development of substudies from the registry. Follow-up health status questionnaires will enable analysis of associations between incident health events and baseline variables.

Narrative responses to the final question on the questionnaire will be analyzed using a deductive approach and thematic content analysis techniques. Multiple investigators will read the narratives provided by participants to perform coding of the significant statements made by participants. After multiple readings, investigators will generate data categories and clusters of statements and will develop themes.

#### Aim 1

We will determine whether essential workers with higher COVID-19 service exposure burden will experience higher rates of stress, depression, anxiety, and substance use than the general population at the time they enroll in CHAMPS, and higher than in similar populations before the COVID-19 pandemic. We will compare exposure by type of service, occupation, and place of service (eg, clinical setting or community), controlling for age, self-reported sex, and race. We will conduct analyses to identify mediators, such as racial status, and moderators, such as proactive coping and resilience.

#### Aim 2

We will determine whether the severity of mental health symptoms will be associated with changes in the prevalence of SARS-CoV-2 infections by geographic region.

#### Aim 3

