We will ascertain whether exposure to COVID-19 service burden will affect physical and mental health over time and how these are influenced by psychosocial variables (eg, stress, depression, anxiety, burnout). We will analyze whether longitudinal health outcomes are associated with type of service; severity and duration of mental health symptoms; and age, sex, race, and other variables. We anticipate that some analyses will depend on the adequacy of the sample sizes in various demographic subgroups.

#### Aim 4

We will obtain longitudinal data to determine whether mental health symptoms will persist longer among participants with more severe symptoms and whether these symptoms will be associated with higher incidence of physical health conditions.

#### Aim 5

We will ascertain the extent to which the thematic contents of the narrative responses to the final question of the questionnaires are correlated with measures of distress (stress, anxiety, depression, burnout) and moderated by measures of resilience. We will ascertain whether thematic content is a moderator or mediator of health outcomes and is associated with retention of participants over time.

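### The service-burden exposure is built mainly from a perceived-stress scale that the plan also calls an outcome of exposure, which compromises Aim 1's comparisons on stress, anxiety and depression

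*Protocol article*

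**What the plan says.** The Exposure Assessment section of the protocol article fixes the exposure: "We will define and quantify exposure to COVID-19 service burden by summing participants’ scores on the Perception of Stress at Work scale", and then "we will add a point to that score for each of several additional stressors". Table 2 gives the first component as the "Perception of Stress at Work scale", scored as "Score of 9-item scale". It adds six yes/no items at one point each: longer hours, a different setting, care of patients with COVID-19, a changed living arrangement, own diagnosis, and a diagnosis in a close contact. No weighting or standardisation is described.

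The next paragraph says that "perceived stress was deemed to be an outcome of exposure, but it can also be included as an exposure variable in models". The sentence goes on to limit that second use to models of the incidence of health conditions over time.

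Under Analysis, Aim 1 asks whether workers with "higher COVID-19 service exposure burden will experience higher rates of stress, depression, anxiety, and substance use than the general population" at enrolment, and higher than similar populations before the pandemic. Aim 3 uses the same exposure: "We will ascertain whether exposure to COVID-19 service burden will affect physical and mental health over time".

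Aim 1 does not name its stress instrument. The Stress paragraph under Measures covers both the IES-R (traumatic stress) and a COVID-19-specific scale. Data Management and Quality lists stress separately from traumatic stress, while the first hypothesis under Objectives names traumatic stress only. Table 1 collects the COVID-19-specific scale, IES-R, GAD-7 and PHQ-2 at baseline, all by self-report; only the last three are repeated in later waves.

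**The concern.** A variable that the plan regards as a consequence of exposure is also the main ingredient of that exposure. Workers who rank high on the score do so partly because they report more stress. Aim 1 then asks whether those workers have more stress, anxiety and depression than external populations. Part of any difference would come from how the group was selected, not from what the pandemic working conditions did. The result could be reported as an effect of COVID-19 service when it is partly the agreement of one self-report of strain with another taken at the same time.

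This is not a detail left to an analysis plan. The article fixes the scoring and states both roles of perceived stress without reconciling them.

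**Working it through.** The protocol gives no numerical result for this score, so there is no figure to reproduce. The check is how much of the score is perceived stress.

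**Inputs from the protocol:** 9 items in the stress scale; six further components at one point each (Table 2).

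**Assumptions, because the protocol does not give them:** item response width k from 1 (0/1) to 4 (0-4 or 1-5); answers spread evenly over the response scale; inter-item correlation r from 0.2 to 0.5; prevalence p of each yes/no stressor from 0.1 to 0.5; correlation rb among the stressors of 0 or 0.2; and no relation between the six stressors and perceived stress.

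**Step 1. Share of the attainable score range,** 9k/(9k + 6):

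- k = 1: 9/15 = 60%
- k = 2: 18/24 = 75%
- k = 3: 27/33 = 82%
- k = 4: 36/42 = 86%

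**Step 2. Share of variance.** Let S be the stress sum and B the sum of the six stressors.

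- Item variance: v = ((k + 1)² − 1)/12
- V_S = 9v(1 + 8r)
- V_B = 6p(1 − p)(1 + 5rb)
- Share = V_S/(V_S + V_B)

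**Step 3. Correlation of the score with perceived stress when the stressors have no effect:** the square root of that share.

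| Case | V_S | V_B | Share | Correlation |
|---|---|---|---|---|
| Lowest with r ≥ 0.2: k = 1, r = 0.2, p = 0.5, rb = 0.2 | 9 × 0.25 × 2.6 = 5.85 | 6 × 0.25 × 2 = 3.00 | 0.66 | 0.81 |
| Four-level items: k = 3, r = 0.2, p = 0.5, rb = 0.2 | 9 × 1.25 × 2.6 = 29.25 | 3.00 | 0.91 | 0.95 |
| Highest: k = 4, r = 0.5, p = 0.1, rb = 0 | 9 × 2 × 5 = 90 | 6 × 0.09 = 0.54 | 0.99 | 0.997 |
| Extreme: k = 1, r = 0, p = 0.5, rb = 0.2 | 9 × 0.25 = 2.25 | 3.00 | 0.43 | 0.65 |

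The share drops below one half only when the 0/1 items are mutually uncorrelated and the stressors are correlated (0.43 at p = 0.5, 0.47 at p = 0.3). The two-thirds floor also depends on evenly spread answers. If 0/1 items were endorsed by only 20%, v = 0.2 × 0.8 = 0.16, V_S = 9 × 0.16 × 2.6 = 3.74, the share is 3.74/6.74 = 0.56 and the correlation is 0.75.

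**Step 4. If stress means the IES-R.** Assume that it correlates 0.3 to 0.5 with perceived work stress and not at all with the six stressors. The score then correlates with it between 0.3 × 0.81 = 0.24 and 0.5 × 0.997 = 0.50. The same arithmetic applies to the GAD-7 or PHQ-2 under the same assumed range.

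**Step 5. Without the stress scale.** The exposure runs from 0 to 6, and its correlation with perceived stress is 0 when the stressors have no effect.

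**The case against.** The strongest defence is that perceived conditions are a deliberate exposure. The fifth hypothesis concerns perceived exposure to adverse working environments, and Measures describes the adapted COVID-19 scales as covering the work environment as well as concerns. The item content is not shown, so the scale cannot be treated as pure distress. This stands in part: perceived conditions may be a legitimate exposure. It does not explain why the same section calls perceived stress an outcome.

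Stronger readings are tempting, and the protocol does not support them:

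- **That Aim 1 regresses stress on the score.** Aim 1 describes comparisons with external populations. The baseline regressions are described separately and openly name work stress as a predictor. Selecting higher-burden workers by the score still affects the external comparison.
- **That a false positive is certain.** The association is built in only if stress includes the COVID-19-specific scale. For the IES-R, GAD-7 or PHQ-2 it depends on an assumed correlation and on taking no effect of the six stressors as the null, which is not the natural null for a score meant to include perceived conditions.
- **That Aim 3 is circular.** The plan expressly allows perceived stress as an exposure for incident conditions. Whether stress precedes later physical illness is a sound prospective question.
- **That own infection cannot be separated from work stress.** The composite merges them, but infection status is asked on its own at enrolment, so the data allow separation.

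The Limitations section does say that the algorithm should be evaluated against an independent data set. That does not address overlap between exposure and outcome.

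**Conclusion.** The point holds for Aim 1 and for any analysis of this score with stress, anxiety or depression as the outcome. The contradiction over the role of perceived stress is in the text and needs no assumption. By attainable range the stress scale is 60% to 86% of the score under every format tried. By variance it is about two thirds or more, with a correlation of about 0.8 or more with perceived stress under no effect of the six stressors; this rests on inter-item correlation of at least 0.2 and evenly spread answers, and is lower in the corner cases shown.

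The fault is identity if Aim 1's stress includes the COVID-19-specific scale, and contamination by a related concurrent measure otherwise. It does not make Aim 3 circular for physical outcomes; there the composite only blurs which component carries an association.

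**What to change.** 1. Reconcile the two paragraphs of Exposure Assessment and state one role for perceived stress in each aim.
2. For Aim 1 and other analyses with stress, anxiety or depression as the outcome, make an index of the factual stressors the primary exposure. Treat the Perception of Stress at Work score as an outcome or mediator.
3. Name the stress instrument in Aim 1. State which items are scored, since Table 1 gives 10 items for COVID-19-specific stress and Table 2 uses a 9-item scale, and give the response format.
4. For the longitudinal incidence models of Aim 3, enter the factual index, perceived stress and own COVID-19 diagnosis as separate terms. The index then holds the other five stressors, so that diagnosis is not counted twice. Report the index with and without perceived stress, because adjusting for a mediator removes the effect that passes through it.
5. Keep the composite only as a labelled sensitivity analysis in those incidence models.

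The components are collected individually, so the cost is rescoring and revised wording, with no new data. The drawback is that the factual index has a narrower range and its associations will probably be smaller.

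### The COVID-19 service-burden exposure includes perceived work stress, which the same section calls an outcome of exposure, so a burden-distress association need not reflect working conditions

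*Protocol article*

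**What the plan says.** In the protocol article, Exposure Assessment opens with "We will define and quantify exposure to COVID-19 service burden by summing" the Perception of Stress at Work scale, and then adds points for further stressors. Table 2 gives the weights. The scale enters in full ("Score of 9-item scale"). Six circumstances enter at "Yes=1 additional point" each: more hours, a different setting, caring for COVID-19 patients, changed living arrangements, own diagnosis, and a close contact's diagnosis.

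The next paragraph of the section states that "perceived stress was deemed to be an outcome of exposure, but it can also be included as an exposure variable in models", the models in question being those for incident health conditions.

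The score is then used in the Analysis section. Aim 1 asks whether "essential workers with higher COVID-19 service exposure burden will experience higher rates of stress, depression, anxiety, and substance use" than comparison populations. Aim 3 asks whether burden affects physical and mental health over time, and "how these are influenced by psychosocial variables (eg, stress, depression, anxiety, burnout". The heading of Table 1 says that all data are self-reported. The adjustment listed for the baseline regressions is sex, age, race/ethnicity and job classification.

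**The concern.** A variable can be an outcome in one model and an exposure in another. It cannot be a component of an exposure and also an outcome of that exposure without making the association partly arithmetic. The only perceived-stress measure that the section names is the one that Table 2 puts into the sum.

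Two things are at stake. First, where perceived stress is the outcome, a score containing it will correlate with it whatever the working conditions do. Second, where the outcome is anxiety, depression or traumatic stress, a person inclined to report distress scores higher on both sides of the model, and the listed covariates do not remove that. In either case an association could be read as an effect of service conditions when it reflects how people report.

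**Working it through.** The article gives no effect size or test result for this analysis, so there is no stated figure to reproduce. The check is how much of the score is perceived stress, and what follows if the six circumstances have no effect.

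**Inputs from the article.** A 9-item scale; six one-point circumstances; 2762 enrolled, of whom 1534 are in the longitudinal cohort; all data self-reported.

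**Assumptions, because the article does not give them.** Item coding, prevalence of the circumstances, and the correlations of a reporting trait with perceived stress and with the outcome.

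**1. Share of the score's range.** The scale contributes 9 × (range per item), the circumstances 6.
- Items coded 0–1: 9/15 = 60%.
- Items coded 0–3: 27/33 = 82%.
- Items coded 0–4 or 1–5: 36/42 = 86%.

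**2. Share of the score's variance.** With P the perceived-stress score, C the circumstance count, and the two independent, the share is Var(P) / (Var(P) + Var(C)). Six independent items at 50% give Var(C) = 6 × 0.25 = 1.5.
- Lowest case, nine uncorrelated 0/1 items at 50%: Var(P) = 9 × 0.25 = 2.25, share 2.25/3.75 = 60%.
- SD of P equal to 3: 9/10.5 = 86%.
- SD of P equal to 6: 36/37.5 = 96%.
- Correlated items (loading 0.6 on one trait, circumstances at 40%), by simulation: about 82%, 97% and 98% for 0–1, 0–3 and 1–5 coding.

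**3. Burden against distress when C has no effect.** The correlation that arises is r = (trait–P correlation) × (trait–outcome correlation) × √(share). The expected test statistic is about r × √(n − 1), and the rejection rate of a two-sided 5% test is about Φ(statistic − 1.96). Take a trait–outcome correlation of 0.6, a trait–P correlation of 0.1 and n = 1534 (√1533 = 39.15).
- Share 86%: r = 0.1 × 0.6 × 0.926 = 0.0555; statistic 2.17; rejection about 59%.
- Share 96%: r = 0.1 × 0.6 × 0.980 = 0.0588; statistic 2.30; rejection about 63%.
- Share 60%: r = 0.1 × 0.6 × 0.775 = 0.0465; statistic 1.82; rejection about 44%.

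Simulation with 4000 runs per setting gave 57%, 64% and 44% in the same order. The circumstance count alone rejected in about 5%. With a trait–P correlation of 0.2, the formula gives 95% to above 99% over the same shares. With a trait–P correlation of zero, the burden test rejected in about 5%.

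**4. A second model at item level.** Here the nine items each load 0.6 on the reporting trait, so perceived stress is much closer to the trait, and the trait–outcome correlation is only 0.1. Burden rejected in 87–95% of null runs at n = 1534 and 99–100% at n = 2762, with mean r of 0.08 to 0.09. The circumstance count stayed at 3–7% in every setting. With a trait–outcome correlation of zero, burden rejected in 3–6%.

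**5. Perceived stress as the outcome.** Its correlation with a total that contains it is √(share) when P and C are independent. Simulated values were 0.90 to 0.99 with correlated items and 0.78 to 0.96 with uncorrelated items, while the correlation of P with C was 0.00.

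**The case against.** The strongest reply is that perception belongs in the construct. The fifth hypothesis under Objectives concerns perceived exposure to adverse working environments, with PPE and staffing as examples, and the Stress section says that the adapted scales assess the work environment. The null in the working treats the nine items as carrying no information about conditions, which the article does not say; the item content is in a source not shown. This stands in part. It means that the six-point count cannot simply replace the score, because it omits PPE and staffing. It does not show that a sum can separate conditions from the reaction to them.

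Four stronger readings are tempting, and the article does not support them.
- *Perceived stress will be entered beside the burden total.* With B = P + C, b_P·P + b_C·C = b_C·B + (b_P − b_C)·P. True effects of 0.05 for P and 0.10 for C would then show as 0.10 on burden and −0.05 on perceived stress, making a harmful factor look protective. The section permits perceived stress as an exposure in incidence models and does not exclude this model, but it does not plan it.
- *The same score is also the influencing variable in Aim 3.* Stress there may mean traumatic stress on the IES-R, which Table 1 schedules repeatedly; the COVID-specific stress scale is scheduled at baseline only. The same uncertainty applies to stress in Aim 1, so the part-whole result is conditional.
- *The baseline regressions have the same fault.* They name "estimates of exposure to COVID-19 infection and COVID-19–related stress at work" openly and do not mention the burden score.
- *Aim 3 will be supported whatever happens.* The bias needs a shared reporting tendency and vanishes without one. Incident physical conditions are less directly circular than baseline distress.

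The Limitations section asks that the algorithm be evaluated on independent data. That is a fair caveat, but it does not mention the overlap, and external evaluation would not remove it. Nor is this detail left to an analysis plan: the article itself fixes the score's composition and states the conflicting roles.

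**Conclusion.** The point holds for the burden score as used in Aims 1 and 3. The article puts perceived stress inside the exposure and calls it an outcome of exposure, and perceived stress probably dominates the sum (about 60% to 98% of variance under the assumed codings). A burden-distress association can therefore arise with no effect of the six circumstances: about 60% rejection at n = 1534 under the modest assumptions above, about 44% at the lowest variance share, and higher with a stronger shared trait.

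The size depends on unstated item coding and on assumed correlations, and on treating the circumstances as unrelated to perceived stress. Given any positive shared reporting tendency, the direction does not depend on these values. The result is firmest for self-reported distress and weaker for incident physical conditions.

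**What to change.** In Exposure Assessment and Table 2, split the score. For Aims 1 and 3, estimate the recorded circumstances (as a count or as separate items) and the Perception of Stress at Work score as separate terms. Then state the following:
- Effects of working conditions are attributed only to the circumstance component. The perceived-stress component is interpreted as perceived exposure, which is what the fifth hypothesis asks about.
- Perceived stress has one declared role in each model. Where it is an outcome or mediator, the circumstance component alone is the exposure.
- The summed score is secondary, and perceived stress is never entered beside a total that contains it.
- Aims 1 and 3 name the instrument meant by stress.

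All items are in the planned data collection, so the cost is analysis wording. The price is a coarser circumstance exposure (0 to 6) with wider intervals, which does not itself capture PPE or staffing. Where both terms are in one model, the circumstance coefficient holds perceived stress fixed, so any effect running through perceived stress has to be read from the circumstance-only model.
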